### Outcomes

The primary clinical outcome will be the overall score achieved in Sniffin Sticks Test (SST) extended version, which objectively assess the olfactory function through the Threshold, Discrimination, and Identification (TDI) score (Hummel et al., 1997). This olfactory test is comprised of three different components: olfactory threshold, odor discrimination, and odor identification. The olfactory threshold represents the level of detection of odors from low to high concentrations, the odor discrimination is the non-verbal distinction between different odors, and odor identification represents the ability to name or associate an odor. Using commercially available felt-tip pens, the odorants will be presented approximately 2 cm in front of both nostrils for 2 s (Hummel et al., 1997, 2007, 2009; Gudziol et al., 2006; Rumeau et al., 2016). Following the previous literature, we have established a 6 points improvement as a significant change (Hummel et al., 2009; Fleiner et al., 2012; Konstantinidis et al., 2013; Schriever et al., 2014; Pekala et al., 2016).

The **functional capacity** will be assessed with Short Physical Performance Battery (SPPB), which assessed balance, gait velocity, and leg strength (from 0 worst to 12 best scale) (Guralnik et al., 1994). In addition, to measure disability, the Barthel Index of independence during activities of daily living (ADLs) at the moment of assessment will be employed. This index ranges from 0 worst to 100 best (Mahoney and Barthel, 1965; van Bennekom et al., 1996). The magnitude of meaningful change (i.e., clinically significant) will be 1 point for SPPB (Perera et al., 2006) and 5 points for the Barthel Index (Shah et al., 1989; van Bennekom et al., 1996). Lastly, the changes in handgrip strength measured with a dynamometer (Takei 5401 Digital Dynamometer) will also be used to assess the functional capacity. The handgrip strength is a powerful predictor of disability (Rantanen et al., 1999), an indicator of overall muscle strength and is associated with a variety of clinically relevant health outcomes in aging adults (McGrath et al., 2018).

**Cognitive function** will be assessed by Mini-mental State Examination (MMSE) one of the most used instrument for screening cognitive impairment. The MMSE assesses domains of orientation, memory, attention, language, and visuospatial ability and is scored out of 30 points. Scores ≤ 23 points are indicative of likely cognitive decline (Folstein et al., 1975; Pi et al., 1994). The Trail Making Test part A (TMT-A) is a neuropsychological test that provides information on visual search, scanning, speed of processing, mental flexibility, and executive functions (Tombaugh, 2004). As the TMT-A is sensitive to a variety of neurological impairments and processes it will be employed to characterize the subjects and to observe changes in the groups that will be assessed at different point in time. The Symbol Digit Modalities Test (SDMT) is easily administered and sensitive to the presence of cerebral dysfunction (Smith, 1973). The score of this test is the number of correct substitutions completed within the time limit, with the maximum score of 110 (Smith, 2002). It is also sensitive to spontaneous recovery of brain functions and to improvements resulting from therapeutic treatments (Smith, 2002; Cancela et al., 2012).

The **nasal exfoliation**, OE cell culture and subsequent quantitative proteomics will be performed in an ISO 9001:2015 quality environment as previously described (Lachén-Montes et al., 2020b; Barrera-Conde et al., 2021). The mass-spectrometry-based comparative protein analysis together with the corresponding bioinformatic phase (pathways and functional interactomes) will be specifically done in the EOT and CA environments (Figure 1).

**FIGURE 1 F1:**
[figure not shown]
Olfactory proteomics workflow to be implemented in parallel with the EOT.

To perform the **Immune characterization**, peripheral blood (PB) samples will be obtained from all groups at baseline and after 12 weeks from CA and EOT groups. EDTA blood collection tubes (Vacuette^®^, Greiner Bio-One) will be used. All PB samples will be processed according to the EuroFlow bulk lysis standard operating protocol (SOP) (available at www.EuroFlow.org). In brief, up to 2 ml of blood will be incubated with 50 ml of ammonium chloride (NH_4_Cl) at room temperature (RT) on a roller bank to lyse non-nucleated red blood cells. After a washing step, cells will be stained for 30 min in the dark with the following BD antibody combination: CD27, CD45RA, CD8, IgD, CD16, CD56, CD4, IgM, CD19, CD3, CD45, and either TCRαβ or preferably TCRγδ, wherein the following antibody pairs CD8/IgD, CD16/CD56, CD4/IgM, and CD19/TCRγδ or CD19/TCRαβ will be conjugated to the same fluorochrome (van Dongen et al., 2019). Finally, cells will be incubated for 10 min (in the dark; RT) with 2 ml of BD FACS™ Lysing Solution (BD Biosciences), washed once and re-suspended in 500 μl PBS prior to acquisition. Data acquisition will be using a BD FACSCanto II. For data analysis, the Infinicyt software (Cytognos, version 2.0) will be used. It provides a data integration and a multidimensional analysis of flow cytometry data.

The **mood status** will be assessed through the 15-item Yesavage Geriatric Depression Scale (GDS-VE), Spanish version, comprising ten affirmative and five negative items (from 0 best to 15 worst scale). The range between 0 and 5 suggest normal results and, scores greater than 5 indicates depression symptoms (Martínez et al., 2002).

**Quality of life** and the economic evaluation will be measured using the Spanish version of the EuroQol 5-Dimension 3-Level questionnaire (EQ5D-3L) (Badia et al., 1999; García-Gordillo et al., 2015). This instrument measures 5 dimensions of health status: mobility, self-care, usual activities, pain/discomfort, and anxiety/depression. In addition, the visual analog scale (VAS) will used to quantify perceived health (from 0, worst health state imaginable; to 100, best health state imaginable).

In order to have a complete phenotyping of subjects, sociodemographic variables (i.e., education level) will be studied. Finally, other end points included will be geriatrics syndromes, Cumulative Illness Rating Scale for Geriatrics (CIRS-G), polypharmacy and International Classification of Diseases (ICD-10). The analysis of all these variables will contribute to characterize the volunteers in the most comprehensive way. The full assessment will last in average 1 h and 20 min.

### Data Analysis

Demographic and outcome data will be summarized for the whole sample and for each group using mean and standard deviation or median and interquartile range for continuous variables and via frequencies and percentages for categorical ones. For the CH group only a descriptive characterization of the measured variables will be performed. In the CA and EOT groups, baseline data will be compared using t-test or Mann-Whitney U test for continuous variables and with chi-square test and Fisher test for categorical ones. For each group, within group pre-post differences will be computed using t-test for dependent samples or Wilcoxon rank sum test. Linear models will be computed in order to compare outcome data between groups, adjusting by baseline outcome data and also by the variables that showed baseline differences.

Further, the association between olfactory level measured with TDI score and marked OE protein modifications (based on fold-change), cognitive, neurological, functional, mood status and quality of life will be analyzed using Pearson or Spearman correlation coefficients. All significant, nearly significant, clinically relevant or potentially confounding variables will be considered in a multiple linear regression model with TDI as dependent variable. In this global model non-significant variables will be removed, which, when eliminated, do not change the estimators of the effect of the rest of the variables in the model. The biochemical analysis, the immune information of each subject and the data associated with pharmacological treatments, fragility, cognition, will also be correlated with olfactory level, with the aim of testing the precision olfactory medicine as a useful tool in the day-to-day context of the Geriatrics Unit. To exclude the effect of sex and age, correlations will be performed as partial correlations, including sex and age as covariates. The statistical analysis will be performed with SPSS (version 26; SPSS Inc., Chicago, IL, United States).

Sample size was calculated based on previous literature (Hummel et al., 2009) on the effects of OT on olfactory function, a medium effect size (*d* = 0.5) and a standard deviation of the outcome of *SD* = 0.8 were assumed (Birte-Antina et al., 2018).

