## Abstract

The aim of this article is to present the research protocol for a prospective cohort study that will assess the olfactory function and the effect of an intervention based on olfactory training in healthy very old adults (≥75 years old). A convenience sample of 180 older people (50% female) will be recruited in three different environments: hospitalized control group (CH) with stable acute illness (*n* = 60); ambulatory control group (CA) of community-based living (*n* = 60); and an experimental odor training group (EOT) from nursing homes (*n* = 60). The odor training (OT) intervention will last 12 weeks. All the volunteers will be assessed at baseline; CA and EOT groups will also be assessed after 12 weeks. The primary end point will be change in olfactory capacity from baseline to 12 weeks period of intervention or control. The intervention effects will be assessed with the overall score achieved in Sniffin Sticks Test (SST) – Threshold, Discrimination, and Identification (TDI) extended version. Secondary end points will be changes in cognitive tasks, quality of life, mood, immune status, and functional capacity. All these measurements will be complemented with an immune fitness characterization and a deep proteome profiling of the olfactory epithelium (OE) cultured *ex vivo*. The current study will provide additional evidence to support the implementation of olfactory precision medicine and the development of immunomodulatory nasal therapies based on non-invasive procedures. The proposed intervention will also intend to increase the knowledge about the olfactory function in very elderly people, improve function and quality of life, and promote the recovery of the health.

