#### Training Protocol

The experimental odor training group (EOT) will be composed by sixty older adults from nursing home. This group will undergo a complete assessment at baseline and after 12 weeks. The training intervention will be performed over a period of 12 weeks and will involve patients exposing themselves once daily to 4 different scents of the four commonly used odors during 20 s each (phenyl ethyl alcohol (PEA): rose, eucalyptol: eucalyptus, citronellal: lemon, and eugenol: cloves). These four odorants were chosen to be representative of four odor categories that tried to identify/represent primary odors (Amoore, 1977; Haehner et al., 2013). These categories are flowery (e.g., rose), foul, fruity (e.g., lemon), aromatic (e.g., cloves), burnt, and resinous (e.g., eucalyptus). Training patients received four vial topaz (total volume 5 ml) with one of the four odors in each (1 ml each, soaked in cotton pads to prevent spilling). All vials will be labeled with the odor name. Patients will be asked to sniff the odors in the morning for approximately 20 s each. Participants will be asked to refrain from smoking, eating, or drinking (except water) during the hour prior to training and testing (Al Aïn et al., 2019). Figure 2 shows a summary outline of the proposed protocol.

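### The non-parametric test named for paired pre-post change is the rank sum test, an independent-samples test: probably a slip for signed-rank, minor, and conservative if followed literally

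*Protocol article*

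**What the plan says.** The Data Analysis section of the protocol article assigns tests to three comparisons:

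- **Ambulatory control against odor training at baseline** (independent groups): "baseline data will be compared using t-test or Mann-Whitney U test for continuous variables".
- **Within each group, before against after** (same people): "within group pre-post differences will be computed using t-test for dependent samples or Wilcoxon rank sum test".
- **Between groups on outcome:** "Linear models will be computed in order to compare outcome data between groups, adjusting by baseline outcome data", and also for variables that differ at baseline.

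The Control and Training Protocol subsections use the same sentence for their respective groups: "This group will undergo a complete assessment at baseline and after 12 weeks". Each of these two groups is planned at 60 people. The hospitalized group is only described at baseline and has no pre-post comparison. The signed-rank test is not named anywhere in the article.

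**The concern.** Baseline and 12-week scores come from the same person and would normally be positively correlated. A paired test works on each person's difference and so removes the between-person variation. The rank sum test pools the two sets of scores and ranks them as if they came from different people. Its reference variance is then too large for paired data whenever the correlation is positive.

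At stake is the non-parametric branch of the within-group tests. That branch may well be used, because several outcomes are bounded scales: the depression scale runs 0 to 15, the SPPB 0 to 12, and the Barthel index up to 100 with entry at 60 or above. Within-group change also has some role in the argument. The Expected Results section anticipates improvement over baseline and discusses an earlier study in older people whose training group showed no significant change from baseline. An analyst who followed the text would run the wrong procedure. One who silently ran the right procedure would depart from the published plan.

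**Working it through.** **1. Which test is named.** With n values at each time, let W be the sum of the ranks of the 12-week values in the pooled sample of 2n. The rank sum test uses W. The Mann-Whitney test uses U = W − n(n+1)/2, which differs from W only by a constant, so the two tests are equivalent. The plan therefore gives one independent-samples test, under two names, to independent data (correctly) and to paired data (incorrectly).

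**2. Inputs for the consequence.** From the article: n = 60 per group. Assumed, because the article does not give them: two-sided 5%, and a pre-post correlation ρ over a range. No figure in the plan depends on this test, so there is none to reproduce.

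**3. Direction and rough size, by a normal approximation.** For unit-SD scores the unpaired standard error of the difference is √(2/n), while the true one is √(2(1−ρ)/n). Hence:

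- Type I error of the unpaired test ≈ 2Φ(−1.96/√(1−ρ)). At ρ = 0.3: 1.96/0.837 = 2.34, giving 1.9%. At ρ = 0.5: 1.96/0.707 = 2.77, giving 0.6%. At ρ = 0.7: 1.96/0.548 = 3.58, giving 0.03%.
- Power for a shift δ, unpaired ≈ Φ((δ√(n/2) − 1.96)/√(1−ρ)); paired ≈ Φ(δ√(n/2)/√(1−ρ) − 1.96). At δ = 0.3, δ√(n/2) = 0.3 × √30 = 1.643. At ρ = 0.7: unpaired (1.643 − 1.96)/0.548 = −0.58, giving 28%; paired 3.00 − 1.96 = 1.04, giving 85%.

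**4. The two rank tests themselves, by simulation.** 20,000 replicates of 60 bivariate normal pairs with unit SD:

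| ρ (assumed) | Type I, rank sum | Type I, signed-rank | Power 0.3 SD, rank sum v signed-rank | Power 0.5 SD, rank sum v signed-rank |
|---|---|---|---|---|
| 0 | 4.8% | 4.8% | 36% v 35% | 75% v 75% |
| 0.3 | 1.9% | 4.8% | 33% v 47% | 79% v 88% |
| 0.5 | 0.6% | 4.7% | 31% v 61% | 83% v 96% |
| 0.7 | 0.07% | 5.0% | 27% v 82% | 89% v 99.8% |
| 0.8 | 0.01% | 4.7% | 24% v 94% | 93% v 100% |

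The two tests agree only when ρ = 0. As ρ rises the rank sum test becomes steadily more conservative. The power gap is wide for small changes and narrow for larger ones.

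**5. Skewed, bounded, tied scores.** These are where the non-parametric option would actually be used. Simulating such scores gave much the same picture: rank sum type I error of about 2% at ρ = 0.3, 0.7% at 0.5 and 0.1% at 0.7. Power for a 0.3 SD change at ρ = 0.7 was about 26% against 76% to 82%, depending on the shape.

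**The case against.** The strongest defence is that the authors meant the paired Wilcoxon test and used the wrong name. The sentence concerns pre-post differences within a group and gives the dependent-samples t-test as the parametric option. One sentence earlier the independent-samples test is called Mann-Whitney U, so the switch to Wilcoxon suggests that a different test was intended. This is persuasive and is the main reason to rate the point minor. It does not make the printed name right.

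Three further points stand:

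- The harm is conditional. The non-parametric branch must be chosen and the phrase then carried out literally.
- With positive correlation the error is conservative, so it would not produce false-positive training effects.
- The group comparison rests on linear models adjusted for baseline, which do not use this test.

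A further objection is that normal data are the case in which the plan would use the t-test, so normal simulations might not apply. This does not stand, because skewed and tied scores behave in much the same way.

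A reader might infer more: that every within-group p-value for skewed outcomes will be wrong, or that the test loses most of its power in general. The article does not support either. It does not show that the test will be run as named, and it gives no correlation. The loss is modest at low correlation or for larger changes. The sample-size statement assumes "a medium effect size (*d* = 0.5) and a standard deviation of the outcome of *SD* = 0.8 were assumed" but does not say that this is a within-group change. Taking 0.5 SD only as an illustration, power at correlation 0.5 is 83% against 96%.

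**Conclusion.** The concern holds as a minor error of specification. The article names an independent-samples test for paired data, most likely by a slip of terminology. Its reach is limited to the non-parametric option for within-group change in the ambulatory control and odor training groups. Taken literally, the named test would under-reject and could miss small real changes, by the amounts tabulated above. Those amounts rest on 60 complete pairs, an assumed two-sided 5% level and an assumed correlation of 0.3 to 0.8. That the test is misnamed rests on none of these assumptions.

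**What to change.** In the Data Analysis section, and in any statistical analysis plan that repeats the sentence, replace Wilcoxon rank sum test with Wilcoxon signed-rank test for the within-group pre-post comparisons. Leave Mann-Whitney U for the baseline comparison between groups, where it is appropriate. The change is one phrase. It alters neither the sample size, the data collected nor the between-group models, and it has no downside.

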In the literature, there is a full consensus stating that sense of smell gradually decreases with age, especially after the age of 60 (Doty et al., 1984; Murphy et al., 2002; Doty et al., 2011; Mullol et al., 2012; Hummel, 2014; Sorokowska et al., 2015; Masala et al., 2018; Doty, 2019; Kondo et al., 2020). In relation to sex differences, by one side Doty et al. (1984) have observed that women outperformed men at all ages in healthy subjects, and a recent meta-analysis has confirmed the female olfactory superiority, although authors emphasized the effect sizes observed were notably small (Sorokowski et al., 2019). By other side, when comparing healthy control subjects with Parkinson’s disease patients, new findings (Melis et al., 2019; Solla et al., 2020) have remarked the importance of sex effect analysis. Regarding smoking, there is no consensus indicating that it accelerates olfactory dysfunction (Vennemann et al., 2008; Fjaeldstad et al., 2021). However, there is evidence that current smoking, but not former smoking, was associated with posttraumatic olfactory loss; namely, a history of smoking was not associated to impairment of olfactory function (Vennemann et al., 2008). Related to lifestyle and behavior factors, the regular exercise was associated with a lower 10-year cumulative incidence of olfactory impairment; in addition, the association with exercise was more robust among those who exercised three or more times per week than among those who only exercised 1–2 times per week (Schubert et al., 2013).

Training and repeated exposure to odorants leads to enhanced olfactory sensitivity (Al Aïn et al., 2019). The olfactory or odor training (OT) is a non-invasive technique with no significant side effects. Previous studies have proven the usefulness of OT in handling olfactory deficits with various etiologies (Hummel et al., 2009; Patel, 2016; Pekala et al., 2016; Al Aïn et al., 2019). The OT may be considered a simple protocol, which has proven efficacy in some patients with olfactory dysfunction. Despite increasing acceptance as an appropriate intervention, questions related to both efficacy and mechanism of action have persisted (Hummel et al., 2009; Turner, 2020).

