## Materials and Methods

### Study Design and Participants

The sample is a convenience sample and is composed by three groups (*N* = 180, 50% females). Sixty hospitalized patients with acute illness (hospitalized control group – CH), sixty ambulatory patients from the community (ambulatory control group – CA) and, sixty from nursing home – the experimental odor training group (EOT). The study follow the principles of the Declaration of Helsinki (World Medical Association, 2013) and was approved by the Complejo Hospitalario de Navarra Clinical Research Ethics Committee on October 21, 2020 (PI_2020/113). All volunteers or their legal representatives will be asked to sign a written informed consent form, also approved in advance by the ethics committee. There will be no financial compensation.

Following the literature procedures (Delgado-Losada et al., 2020) all the volunteers will be previously evaluated by an expert otolaryngologist including anamnesis and nasal endoscopic examination to exclude the possibility of an otorhinolaryngology alteration or pathology that may modify the results of the olfactory test. Therefore, sinusitis, prior nasal surgery, nasal polyps, presence of nasal congestion at the moment of test administration or recent upper respiratory tract infection within two weeks, medication intake with repercussion in olfactory performance or to have reported COVID-19 compatible smell symptomatology are exclusion criteria.

The inclusion criteria are: (i) ≥ 75 years old; (ii) compliance with testing procedure; (iii) Mini-Mental State Examination (MMSE) equal to or greater than 21 points (Pi et al., 1994; Ostrosky-Solís et al., 2000; Reyes-de-Beaman et al., 2004); (iv) Barthel index ≥ 60; (v) participants from acute hospitalized group must be clinically stable. The exclusion criteria are positive diagnosis of any kind of neurodegenerative disease and/or nasosinusal pathology (described before).

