### Intervention

#### Control

The control group will be composed by sixty ambulatory patients from the community (CA). This group will undergo a complete assessment at baseline and after 12 weeks. The volunteers of CA group will receive usual health care assistance; therefore they will not participate in any kind of olfactory training.

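### Covariates for the EOT-CA comparison are chosen by baseline difference, so real confounders in non-randomised groups can be left out; the likely bias is modest, and fixing the set in advance costs little

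*Protocol article*

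**What the plan says.** All references are to the protocol article.

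- **Study Design and Participants:** "The sample is a convenience sample and is composed by three groups". Allocation follows care setting and is not randomised. Under Training Protocol, "The experimental odor training group (EOT) will be composed by sixty older adults from nursing home"; under Control, the comparison group is sixty ambulatory people living in the community.
- **Data Analysis, baseline:** for CA and EOT, "baseline data will be compared using t-test or Mann-Whitney U test for continuous variables and with chi-square test and Fisher test for categorical ones". No significance threshold is printed.
- **Data Analysis, main comparison:** the between-group linear models are fitted "adjusting by baseline outcome data and also by the variables that showed baseline differences". Only the baseline outcome is fixed in advance.
- **Data Analysis, associations:** sex and age are forced into the correlations as partial-correlation covariates. Clinically relevant or potentially confounding variables are considered in a separate regression on TDI. Neither provision is extended to the EOT-CA comparison.
- **Introduction:** the article reports that the "sense of smell gradually decreases with age, especially after the age of 60", that women do better than men by a small margin, and that "the regular exercise was associated with a lower 10-year cumulative incidence of olfactory impairment". On smoking it reports no consensus.

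**The concern.** A baseline test asks whether the data show an imbalance. It does not ask whether the variable confounds the comparison. A factor that matters for smell and differs moderately between groups can fail the test and be dropped, while an irrelevant variable that differs by chance is kept.

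This matters more here than in a randomised trial. The groups come from different care settings, so real differences are expected, and covariate adjustment is the only protection against confounding that the article describes for its primary endpoint. The exploratory correlations are guaranteed adjustment for age and sex; the main comparison is not. This is a stated rule rather than a detail left open, so a later analysis plan would have to depart from it, not merely complete it.

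**Working it through.** **Inputs from the article.** 60 per group in EOT and CA; baseline outcome always adjusted for; other variables only if different at baseline. The 60 is taken as given: the point does not depend on how it was derived.

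**Assumed inputs.** Screening at two-sided 0.05; the size of the imbalances; the effect of each factor. None of these is in the article.

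**Step 1. How often the screen flags a real imbalance.** The standard error of a standardised mean difference is √(1/60 + 1/60) = 0.183, so a variable is flagged when the observed difference exceeds about 1.98 × 0.183 = 0.362 SD. Two-sample t-test power:

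| True imbalance | Flagged | Missed |
|---|---|---|
| 0.2 SD | 19% | 81% |
| 0.3 SD | 37% | 63% |
| 0.4 SD | 58% | 42% |
| 0.5 SD | 78% | 22% |
| 0.8 SD | 99% | 1% |

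For proportions, 50% vs 65% is flagged 38% of the time and 10% vs 20% is flagged 33%.

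**Step 2. How much imbalance stays uncorrected.** For a true imbalance of 0.3 SD, the average imbalance left in the model is 0.3 × P(not flagged) − 0.183 × φ((0.362 − 0.3)/0.183) = 0.3 × 0.632 − 0.183 × 0.377 = 0.190 − 0.069 = 0.121 SD, about 40% of the original.

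**Step 3. Bias when factors act on the level of smell only.** Take four independent factors, each 0.3 SD lower in EOT and each worth 0.3 SD of TDI at both visits, with residual pre-post correlation r and no training effect. Once baseline TDI is in the model, each factor's remaining effect is 0.3 × (1 − r). The approximate bias is 4 × 0.3 × (1 − r) × 0.121:

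- r = 0.5: 4 × 0.15 × 0.121 = 0.073
- r = 0.7: 4 × 0.09 × 0.121 = 0.044
- r = 0.8: 4 × 0.06 × 0.121 = 0.029

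Simulation (4,000 runs) gives slightly less, because baseline TDI also carries information about the dropped factors: about 0.06, 0.04 and 0.02 SD, with rejection rates of 6.0%, 5.4% and 5.4%.

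**Step 4. Bias when factors also affect 12-week change.** With baseline carry-over of 0.6 and a further effect per factor of 0.2 to 0.3 at follow-up, simulated bias is about 0.08 to 0.11 SD. Rejection rates lie between about 7% and 11%, depending on the exact set-up. With a further effect of only 0.1, bias is about 0.04 and rejection 5.6%.

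**Step 5. Fixed adjustment in the same scenarios.** With all four factors always included, bias is about 0 and rejection about 5%. Precision is not lost: in the Step 4 set-up the mean standard error is 0.156, against 0.156 to 0.173 under screening.

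**The case against.** The strongest reply is that the rule already contains its main safeguard. Baseline TDI is always in the model, and the Introduction's evidence concerns the level of smell by age and sex, and 10-year incidence for exercise. The article does not show that these factors drive change over 12 weeks. If they act on level only, rejection stays at 5–6%. This stands, and it is why the size given here is modest.

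Nursing-home and community groups may also differ so strongly that the screen works: at 0.8 SD it flags 99%, and the bias is then about 0. A single weak confounder does little harm. The target of 50% females would limit sex imbalance if it is met within each group, which the text does not say. All of this stands, but none of it is a reason to let a test choose the covariates.

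Four stronger readings are tempting and not supported:

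- **That known determinants are left out.** They can be; whether they are depends on imbalances not yet known.
- **That the rule favours a false claim of benefit.** The direction follows the imbalance. If EOT is worse on these factors, nearly all the excess rejections favour control.
- **That selection makes the reported standard errors too small.** In simulation they were close to the empirical ones; the harm is bias.
- **That the protocol names current smoking as a general determinant of smell.** It reports no consensus and links current smoking to posttraumatic loss only.

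**Conclusion.** The concern holds in a limited form. The rule can drop real confounders from the main comparison of non-randomised groups, and moderate imbalances of 0.3 to 0.4 SD are missed between 63% and 42% of the time. The consequence is a residual bias of about 0.02–0.06 SD if the factors act on level only, and about 0.08–0.11 SD if they also affect 12-week change. These sizes rest on the assumed 0.05 threshold, four independent factors, 0.3 SD imbalances and 0.3 SD effects, and would change with them.

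The clause should be fixed, but it does not by itself undermine the trial. A reader might infer that a better covariate list would make the EOT-CA contrast a clean estimate of the training effect. It would not: care setting and intervention coincide completely, so no adjustment can separate them.

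**What to change.** Replace the clause on baseline differences with a covariate set that is fixed before outcome data are seen and used whatever the baseline p-values:

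- **Core:** baseline value of the outcome, age and sex. Data Analysis already treats age and sex as covariates in the correlations.
- **Short addition, chosen on prior knowledge from measures already planned:** for example MMSE, SPPB as the single functional measure, CIRS-G and education.

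Keep the baseline comparison of CA and EOT descriptive and do not use its tests to select covariates. State as a limitation that adjustment cannot remove confounding by care setting.

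The cost is a change of analysis wording and a few degrees of freedom out of 120 participants (six for the example set beyond the baseline outcome, if each variable enters as one term). Sample size and data collection are unchanged.
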